### Protection of human participants and assessment of safety

#### Protection of human participants

The GHC Institutional Review Board (IRB) approved this study.

#### Safety monitoring

This trial will be monitored for safety by an independent Data and Safety Monitoring Board (DSMB) composed of a primary care physician experienced in mindfulness, a biostatistician and a clinical psychologist with experience in treating patients with chronic pain.

#### Adverse experiences

We will collect data on adverse experiences (AEs) from several sources: (1) reports from the CBT and MBSR instructors of any participants’ experiences of concern to them; (2) the 8-, 26- and 52-week CATI follow-up interviews in which the participants are asked about any harm they felt during the CBT or MBSR treatment and any serious health problems they had had during the respective time periods; and (3) spontaneous reports from participants. The project coinvestigators and a GHC primary care internist will review AE reports from all sources weekly. Any serious AEs will be reported promptly to the GHC IRB and the DSMB. AEs that are not serious will be recorded and included in regular DSMB reports. Any identified deaths of participants will be reported to the DSMB chair within 7 days of discovery, regardless of attribution.

#### Stopping rules

The trial will be stopped only if the DSMB believes that there is an unacceptable risk of serious AEs in one or more of the treatment arms. In this case, the DSMB can decide to terminate one of the arms of the trial or the entire trial.

### Statistical issues

#### Sample size and detectable differences

Our sample size was chosen to ensure adequate power to detect a statistically significant difference between each of the two mind–body treatment groups and the usual care group, as well as power to detect a statistically significant difference between the two mind–body treatment groups. Because we considered patient activity limitations to be the more consequential of our two co–primary outcome measures, we based our sample size calculations on the modified RDQ [30]. We specified our sample size on the basis of the expected percentage of patients with a clinically meaningful improvement measured with the RDQ at the 26-week assessment (that is, at least 30% relative to baseline) [57].

Because of multiple comparisons, we will use Fisher’s protected least significant difference test [86], first analyzing if there is any significant difference among all three groups (using the omnibus *χ*^2^ likelihood ratio test) for each outcome and each time point. If we find a difference, we will then test for pairwise differences between groups. We will need 264 participants (88 in each group) to achieve 90% power to find either mind–body treatment different from usual care on the RDQ. This assumes that 30% of the usual care group and 55% of each mind–body treatment group will have clinically meaningful improvement on the RDQ at 26 weeks, rates of improvement that are similar to those we observed in a similar back pain population in an evaluation of complementary and alternative treatments for back pain [87]. We will have at least 80% power to detect a significant difference between MBSR and CBT on the RDQ if MBSR is at least 20 percentage points more effective than CBT (that is, 75% of the MBSR group versus 55% of the CBT group).

Our other co–primary outcome is the pain bothersomeness rating. With a total sample size of 264 participants, we will have 80% power to detect a difference between a mind–body treatment group and usual care on the bothersomeness rating scale, assuming that 47.5% of usual care and 69.3% of each mind–body treatment group have 30% or more improvement from baseline on the pain bothersomeness rating scale. We will have at least 80% power to detect a significant difference between MBSR and CBT on the bothersomeness rating scale if MBSR is at least 16.7 percentage points more effective than CBT (that is, 87% of the MBSR group versus 69.3% of the CBT group).

When analyzing the primary outcomes as continuous measures, we will have 90% power to detect a 2.4-point difference between usual care and either mind–body treatment on the modified RDQ scale scores and a 1.1-point difference between usual care and either mind–body treatment on the pain bothersomeness rating scale (assumes normal approximation to compare two independent means with equal variances and a two-sided *P* = 0.05 significance level with standard deviations of 5.2 and 2.4 for RDQ and pain bothersomeness measures, respectively [88]. Assuming an 11% loss to follow-up (slightly higher than that found in our previous back pain trials), we plan to recruit a sample of 297 participants (99 per group).

Both of the co–primary outcomes will be tested at the *P* < 0.05 level at each time point because they address separate scientific questions. Analyses of both outcomes at all follow-up time points will be reported, imposing a more stringent requirement than simply reporting a sole significant outcome.

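### The 90% power for 2.4 RDQ points and 1.1 bothersomeness points does not hold at 88 analysable per arm, and the printed 16.7 percentage points should be 17.7

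*Protocol article*

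**What the plan says.** All the figures are in the protocol article under Sample size and detectable differences.

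- **Sample size.** The binary RDQ outcome (30% versus 55% improved, 90% power) sets 264 participants, 88 per group. After an allowance for 11% loss, "we plan to recruit a sample of 297 participants (99 per group").
- **Binary bothersomeness.** The n is named: "With a total sample size of 264 participants, we will have 80% power" for 47.5% versus 69.3%. For MBSR against CBT, at least 80% power is claimed on this condition: "at least 16.7 percentage points more effective than CBT (that is, 87% of the MBSR group versus 69.3% of the CBT group").
- **Continuous outcomes.** For activity limitations, "we will have 90% power to detect a 2.4-point difference between usual care and either mind–body treatment on the modified RDQ scale scores". The bothersomeness counterpart, claimed at the same power, is 1.1 points. The method "assumes normal approximation to compare two independent means with equal variances"; the test is at "a two-sided *P* = 0.05 significance level", and the SDs are 5.2 and 2.4. No n is named.

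Elsewhere, Co–primary outcome measures makes the responder comparison the primary endpoint analysis and the mean differences a secondary one. Primary analyses expects at least 89% follow-up, in which case the analysis is complete-case. It also plans adjustment for the baseline value of the outcome, sex and age.

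**The concern.** The binary calculations rest on the number left after loss to follow-up. The two continuous statements come next with no n of their own, so a reader will take them to refer to the same 88 per arm. They do not reproduce there, but they do at the recruited 99. If so, one section mixes power before and after loss without saying so.

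The bothersomeness sentence for MBSR versus CBT contradicts itself, because the stated difference is not the difference between the two rates printed beside it.

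Both slips make the trial look a little more sensitive than the stated inputs allow. The 2.4 and 1.1 points are the only sensitivity figures given for the mean-difference analyses. The 16.7 points belongs to the responder analysis of a co-primary outcome in the aim 2 comparison. A non-significant result would be read against these numbers.

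**Working it through.** **Inputs (Sample size and detectable differences).** Two-sided alpha 0.05 (z = 1.960); SDs 5.2 and 2.4; differences 2.4 and 1.1; 88 analysable and 99 recruited per arm. The inflation is consistent: 99 × 0.89 = 88.1.

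**1. Continuous outcomes, by the stated method**

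Power = Φ(δ / (SD × √(2/n)) − 1.960). The difference detectable with 90% power is (1.960 + 1.282) × SD × √(2/n).

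The printed figures reproduce at n = 99:
- RDQ: SE = 5.2 × √(2/99) = 0.739; 2.4/0.739 − 1.960 = 1.287; power 90.1%.
- Bothersomeness: SE = 2.4 × √(2/99) = 0.341; 1.1/0.341 − 1.960 = 1.265; power 89.7%.

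At n = 88:
- RDQ: SE = 5.2 × √(2/88) = 0.784; 2.4/0.784 − 1.960 = 1.10; power 86.5%.
- Bothersomeness: SE = 2.4 × √(2/88) = 0.362; 1.1/0.362 − 1.960 = 1.08; power 86.0%.

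| n per arm | RDQ: power for 2.4 | RDQ: 90% difference | Bothersomeness: power for 1.1 | Bothersomeness: 90% difference |
|---|---|---|---|---|
| 88 | 86.5% | 2.541 | 86.0% | 1.173 |
| 99 | 90.1% | 2.396 | 89.7% | 1.106 |

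Rounded to one decimal, 99 per arm gives the printed 2.4 and 1.1, and 88 per arm gives 2.5 and 1.2. Strictly, 90% power for 2.4 and 1.1 points needs 99 and 101 analysable per arm.

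Alternatives checked at 88 per arm:
- A t distribution gives 86.1% and 85.6%.
- A one-sided test gives 92.2% and 91.9%, and contradicts the stated two-sided level.
- Rounding does not rescue the RDQ figure: 2.449 points with SD 5.15 gives 88.4%. Bothersomeness reaches 90% only with both inputs at their limits (1.149 points, SD 2.35).

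**2. Binary bothersomeness, MBSR versus CBT**

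87.0 − 69.3 = 17.7, not 16.7.

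Power without continuity correction = Φ((d − 1.960 × √(2p̄(1−p̄)/n)) / √((p1(1−p1) + p2(1−p2))/n)), where p̄ is the mean of the two rates. The correction subtracts 1/n from d.

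At n = 88, 69.3% versus 87%:
- Without correction: (0.177 − 0.1221)/0.0609 = 0.902; power 81.7%.
- With correction: (0.177 − 0.0114 − 0.1221)/0.0609 = 0.715; power 76.3%.

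At n = 88, a literal 16.7 points (69.3% versus 86.0%):
- Without correction: (0.167 − 0.1231)/0.0615 = 0.714; power 76.2%.
- With correction: power 70.2%.

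The smallest difference above 69.3% with 80% power at 88 per arm is 17.4 points without correction and 18.4 with it.

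**3. Which test lies behind the binary figures?** The two comparisons with usual care (30% versus 55% at 90% power, 47.5% versus 69.3% at 80%) each need exactly 88 per arm with continuity correction. The RDQ comparison of MBSR with CBT (55% versus 75%) has 80.0% power at 88 without correction and 75.1% with it. No single choice reproduces the whole set, and the article names none.

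**The case against.** The strongest defence is that little depends on these figures. The sample size comes from the binary RDQ outcome, and its 88 per arm reproduces. The mean comparisons are secondary. The restated differences move by only 0.14 points on a 0 to 23 scale and 0.07 on a 0 to 10 scale. All of this stands.

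A second defence is that the planned model adjusts for the baseline outcome. A baseline-to-follow-up correlation of about 0.33 (RDQ) or 0.35 (bothersomeness) would restore 90% at 88 per arm. That correlation is not in the article, and the stated calculation compares unadjusted independent means, so the defence does not rescue the printed figures. It does block a stronger inference that a reader might draw, that the planned analysis lacks the claimed sensitivity. The documents do not settle that: adjustment could raise power, while clustering within treatment cohorts and the requirement for a significant omnibus test could lower it.

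Third, a reader might take it as established that 99 per arm was used. No n is stated for the continuous figures. The match at 99 and the mismatch at 88 make it a strong inference, but no more.

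Fourth, a reader might conclude that the claim of at least 80% power for MBSR versus CBT on bothersomeness is false. That requires reading 16.7 literally and replacing the printed 87% with 86.0%, which appears nowhere in the article. At the printed rates the claim holds without continuity correction and fails with it. The subtraction error is certain; a power failure is not.

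**Conclusion.** The point holds as a correction to stated figures. By the article's own method, 2.4 RDQ points and 1.1 bothersomeness points carry about 86% power at 88 analysable per arm, roughly 4 percentage points below the 90% claimed. This rests on about 88 per arm being analysed, which follows from the 264 participants, the 11% loss and the complete-case analysis at about 89% follow-up. The 16.7 percentage points contradicts its own sentence and should read 17.7; whether the 80% claim then holds depends on the unnamed test (81.7% or 76.3%).

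The consequence is modest. A reader might infer that the trial is too small, but the documents do not support that: the 88 per arm behind the primary responder analysis of the RDQ, and the 297 to be recruited, are not affected.

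**What to change.** 1. Restate the continuous figures at 88 per arm: 90% power for about 2.5 RDQ points and 1.2 bothersomeness points, or about 86% power for 2.4 and 1.1. Name the n in the sentence.
2. Change 16.7 to 17.7 percentage points, to agree with 87% versus 69.3%.
3. Name the test behind the two-proportion power figures, including whether a continuity correction was used. If it was, the claim of at least 80% power for 17.7 points at 88 per arm must be revised to about 76%, or the difference raised to about 18.4 points.

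The cost is wording only. Design, recruitment target and analysis do not change, and the stated sensitivity becomes slightly less favourable.

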### Statistical analyses

#### Primary analyses

In our comparisons of treatments based on the outcome measures, we will analyze outcomes assessed at all follow-up time points in a single model, adjusting for possible correlation within individuals and treatment group cohorts using generalized estimating equations [89]. Because we cannot reasonably make an assumption regarding constant or linear group differences over time, we will include an interaction term between treatment groups and time points. We plan to adjust for baseline outcome values, sex and age, as well as other baseline characteristics found to differ significantly by treatment group or follow-up outcomes, to improve precision and power of our statistical tests. We will conduct the following set of analyses for both the continuous outcome score and the binary outcome (clinically significant change from baseline), including all follow-up time points (4, 8, 26 and 52 weeks). The MBSR treatment will be deemed successful only if the 26-week time point comparisons are significant. The other time points will be considered secondary evaluations.

We will use an intent-to-treat approach in all analyses; that is, the assessment of individuals will be analyzed by randomized group, regardless of participation in any classes. This analysis minimizes biases that often occur when participants who do not receive the assigned treatments are excluded from analysis. The regression model will be in the following general form:

$$\begin{array}{ll} g\left(y_{t}\right)= & \beta_{0}+\beta_{1}\left(\mathrm{baseline}\right)+\alpha_{1}\left(\mathrm{treatment}\right)+\alpha_{2}\left(\mathrm{time}\right)\\ & +\alpha_{3}\left(\mathrm{treatment}\right)\times \mathrm{time}+\alpha_{4}z+\epsilon , \end{array}$$

where *y*_t_ is the response at follow-up time *t*, *baseline* is the prerandomization value of the outcome measure, *treatment* includes dummy variables for the MBSR and CBT groups, *time* is a series of dummy variables indicating the follow-up times and *z* is a vector of covariates representing other variables adjusted for. (Note that α_1_, α_2_, α_3_ and α_4_ are vectors.) The referent group in this model is the usual care group. For binary and continuous outcomes, we will use appropriate link functions (for example, logit for binary). For each follow-up time point at which the omnibus *χ*^2^ test is statistically significant, we will go on to test whether there is a difference between MBSR and usual care to address aim 1 and a difference between MBSR and CBT to address aim 2. We will also report the comparison of CBT to usual care. When determining whether MBSR is an effective treatment for back pain, we will require that aim 1, the comparison of MBSR to usual care, must be observed.

On the basis of our previous back pain trials, we expect at least an 89% follow-up and, if that holds true, our primary analysis will be a complete case analysis, including all observed follow-up outcomes. However, we will adjust for all baseline covariates that are predictive of outcome, their probability of being missing and differences between treatment groups. By adjusting for these baseline covariates, we assume that the missing outcome data in our model are missing at random (given that baseline data are predictive of missing data patterns) instead of missing completely at random. We will also conduct sensitivity analysis using an imputation method for nonignorable nonresponses to evaluate whether our results are robust enough to compensate for different missing data assumptions [90].

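### The primary complete-case GEE conditions missingness on baseline covariates only, so the 26-week difference can be biased if loss depends on early response differently by arm

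*Protocol article*

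**What the plan says.** All statements are in the protocol article, under Primary analyses.

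- **Model.** The article says "we will analyze outcomes assessed at all follow-up time points in a single model, adjusting for possible correlation within individuals and treatment group cohorts", by GEE. The binary and continuous outcomes are both analysed in this way, "including all follow-up time points (4, 8, 26 and 52 weeks" being the stated scope.
- **Missing data.** Retention is dealt with conditionally: "we expect at least an 89% follow-up and, if that holds true", then "our primary analysis will be a complete case analysis, including all observed follow-up outcomes".
- **Assumption.** "By adjusting for these baseline covariates, we assume that the missing outcome data in our model are missing at random", and the reason given in parentheses is "given that baseline data are predictive of missing data patterns) instead of missing completely at random".
- **Sensitivity.** "We will also conduct sensitivity analysis using an imputation method for nonignorable nonresponses".

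The primary endpoint is the binary one, at least 30% improvement at 26 weeks (Co-primary outcome measures). Table 4 shows both co-primary outcomes collected at baseline, 4, 8, 26 and 52 weeks. The working correlation is not stated.

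**The concern.** Missing at random allows missingness to depend on anything observed, including earlier outcomes. The assumption described in the article is narrower: missingness depends only on the baseline covariates in the model. The two differ when people who have not improved by week 4 or 8 are more likely to be missing at week 26.

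An unweighted GEE gives valid estimates under the narrower assumption but not, in general, under the wider one. Putting early outcomes into the model as responses does not by itself repair this. How far they help depends on the working correlation, and for a binary outcome even a correlated structure need not remove the bias.

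Dropout could plausibly differ by arm here. Two arms ask for eight 2-hour sessions plus home practice and the third does not, and participants know whether they have classes. If early non-responders are lost more in a class arm than in usual care, the class arm's observed responder rate is too high and the contrast with usual care is inflated. The documents give no dropout figures by arm, so this is a possibility and not a forecast.

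**Working it through.** **The plan's own figures.** Under Sample size and detectable differences the article gives 30% v 55% response, 90% power, 88 per group and 11% loss.

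- Two proportions, two-sided 0.05: n = [1.96√(2·0.425·0.575) + 1.2816√(0.30·0.70 + 0.55·0.45)]² / 0.25² = (1.370 + 0.867)² / 0.0625 = 80.1, so 81 per group. The continuity correction gives 87.9, so 88, which reproduces the article.
- 264 / 0.89 = 296.6, so 297, also reproduced.
- Standard error of the difference at 88 per group: √[(0.21 + 0.2475)/88] = 0.072, or 7.2 points. This ignores covariate adjustment and class clustering.

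**Hand calculation of the bias in one arm.** Let q be the share of early responders, d1 and d0 the loss among early responders and non-responders, and p1 − p0 the gap between them in 26-week response. The observed responder rate is shifted by

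(p1 − p0) × [ q(1 − d1) / {q(1 − d1) + (1 − q)(1 − d0)} − q ].

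Assume d0 = 18% and d1 = 4%. Overall loss of 11% then requires q = 0.5. The bracket is 0.48/0.89 − 0.5 = 0.039. With an assumed latent correlation of 0.7 between weeks 8 and 26 and even splits, p1 − p0 = (2/π)·arcsin(0.7) = 0.49. The shift is 0.039 × 0.49 = 0.019, about 2 points. This is the bias in the contrast if loss in the comparator is random and the early scores contribute nothing.

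**Simulation of the planned type of model.** The simulation had two arms of 20,000, RDQ SD 5.2 and a true 26-week difference of about −2.4 RDQ points. About 11% per arm were lost after week 8, with log-odds of loss 1 per SD of the 8-week score. The model had treatment by time plus baseline score. The correlations between visits (0.4 to 0.75) and the dropout strength are assumptions. Entries are the 26-week responder difference in percentage points, with the bias against full data in brackets (differences taken before rounding).

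| Dropout mechanism | Full data | Independence | Exchangeable | Unstructured |
|---|---|---|---|---|
| Alike in both arms | 19.9 | 20.1 (+0.2) | 19.9 (0.0) | 20.0 (+0.1) |
| Early non-responders lost in MBSR only | 19.1 | 21.3 (+2.1) | 19.7 (+0.6) | 19.7 (+0.6) |
| Opposite in the two arms (extreme) | 20.0 | 24.3 (+4.3) | 21.2 (+1.2) | 21.2 (+1.3) |

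For the continuous RDQ score, the second and third rows give a bias of 0.27 and 0.50 points under independence, and at most 0.04 under the correlated structures. The residual problem is therefore mainly in the binary endpoint, which is the primary one.

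A coarser simulation used 30,000 per arm, binary outcomes and the 18%/4% split, with no baseline covariates described. Its observed-case differences exceeded the truth by 1.0, 2.2 and 4.0 points when usual-care loss ran in the same direction, at random or in the opposite direction (26.4 v 25.4, 27.8 v 25.6, 29.3 v 25.3). Standardising on week-8 response within arm gave 25.5, 25.8 and 25.3, which removes nearly all of it.

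**Against sampling error.** 2.1/7.2 = 0.29 and 4.3/7.2 = 0.60 standard errors under independence; 0.6/7.2 = 0.08 and 1.2/7.2 = 0.17 under exchangeable correlation. If loss reached about 20%, the MBSR-only case under independence grows to 22.5 − 19.2 = 3.3 points.

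**The case against.** A reader might infer that the plan discards the 4- and 8-week data. It does not. They are responses in the same GEE, and the article's complete-case analysis retains every observed follow-up outcome. They say nothing about missing 26-week values only under an independence working correlation. The article names no structure, and the analysis plan may name one.

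A reader might also infer that the treatment difference is biased outright. That does not follow either. Material bias needs a mechanism that differs by arm, and the documents give no evidence of one. The article itself anticipates disappointment in usual care and pays $50 to offset it, so unimproved usual-care participants may be lost too, which moves towards the near-zero case.

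Leaving the classes is not the same as a missing outcome. The section on data collection says outcomes are sought from everyone, including those who never attend. Telephone non-responders are mailed a short form with only the two primary outcomes. The model also adjusts for baseline predictors of outcome and missingness, and a nonignorable analysis is planned.

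All of this stands, and it limits the size of the problem. It does not supply an analysis built to be valid when loss depends on observed early response. The nonignorable analysis addresses dependence on unobserved values, and good retention reduces the amount of missing data without changing the assumption. The lack of a stated fallback below 89% follow-up is no finding in itself, since the analysis plan may hold it.

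**Conclusion.** The point holds in a limited form. The article presents missingness given baseline covariates as missing at random, and its primary analysis is not generally valid under the wider assumption that the 4- and 8-week data would support. The 26-week responder difference can be biased if loss depends on early response and does so differently by arm.

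At about 11% loss the bias is about 2 percentage points (about 4 in the extreme case) with an independence working correlation. It is about 0.6 to 1.2 points with an exchangeable structure, and unstructured is within 0.1 of that. It is close to nothing when dropout acts alike in all arms. These sizes rest on assumed correlations, dropout strengths and arm differences, and on a working correlation that the article does not state. Against a planned difference of 25 points and a standard error near 7.2, the bias would seldom decide the result. It is still avoidable with data that the trial already collects in every arm, so the change should be made.

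**What to change.** Whatever the follow-up rate, base the 26-week estimate on a missing-at-random analysis that uses the early scores. Either route will do:

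- **Multiple imputation.** Impute RDQ and bothersomeness scores by arm from the baseline covariates and the observed follow-up scores, including weeks 4 and 8, allowing for class cohort. Then derive the 30% responder status and fit the planned GEE.
- **Weighting.** Fit the same GEE with inverse-probability weights from a model for being observed that includes the 4- and 8-week outcomes.

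Reword the assumption so that it says missingness may depend on baseline covariates and observed earlier outcomes, and state the working correlation. Keep the observed-case GEE and the nonignorable analysis as sensitivity analyses.

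The cost is wording, modest programming and reliance on an imputation or weighting model. For anyone lost before week 4 there are no early scores to use, so the gain is confined to later loss.
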